# 6.0 BASELINE EVALUATION AND TREATMENT ALLOCATION

## 6.1 Baseline evaluation and procedures

On day 0, patients fulfilling the selection criteria will be assigned a study number and will undergo a complete history and physical examination (Appendix 9). Patients will be referred to the laboratory to obtain a fingerprick blood sample for repeat thick blood smear, thin blood smear, haemoglobin measurement and to save of filter paper for future molecular testing. After going to the laboratory, the patients will be referred to the study nurse for treatment.

## 6.2 Treatment group assignment

Patients will be randomly assigned to one of the two treatment groups (AQ+AS or coartemether). Randomization will be done according to a pre-determined randomization list. Treatment allocation and administration of medications will be performed by the study nurse.

## 6.3 Treatment allocation

To allocate subjects to the appropriate treatment group, the study nurse will select the next available treatment number and corresponding study regimen. The study nurse will record the data and time of treatment assignment and the patient's study number.

## 6.4 Study intervention

**Table 3. Drug formulation and labelling**

| **Drug** | **Trade name (Manufacturer)** | **Class** |
| --- | --- | --- |
| Amodiaquine (200mg base) | Camoquin (Parke-Davis) | 4-aminoquinoline |
| Artesunate (50mg) | Arsumax (Sanofi) | artemisinin derivative |
| Artemether + lumefantrine  (20mg/120 mg) | Coartem (Novartis) | artemisinin derivative + dibutyl-aminoethanol |

### 6.4.1 Dosing of study medications

All subjects will receive two medications in the morning and one medication in the evening for 3 days. Subjects randomized to the AQ+AS group will receive AQ and AS in the morning and lactose placebo tablets in the evening. AQ will be given as 25 mg/kg over 3 days (10 mg/kg on day 0, 10 mg/kg on day 1, and 5 mg/kg on day 2) and AS will be given as 12 mg/kg over 3 days (4 mg/kg/day). AQ+AS subjects will also be given lactose placebo tablets given in the evening over 3 days, dosed similarly to weight-based guidelines for coartemether. Subjects randomized to the coartemether group will receive coartemether twice daily for 3 days, given in fixed dose tablets (20 mg artemether + 120 mg lumefantrine) according to weight-based guidelines. Coartemether subjects will also be given lactose placebo tablets in the morning for 3 days, dosed similarly to weight-based guidelines for AQ. Details of the dosing schedule are included in Appendix 6.

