## 6.5 Treatment administration and blinding

Study medications will be administered according to weight-based guidelines (Appendix 6). Study medications will not be identical in appearance or taste, but the number of doses received will be similar (2 different medicines in the morning, 1 medicine in the evening) for patients in both treatment groups. Patients will not be informed of their treatment regimen, and all study staff involved in the assessment of patient outcomes, including the study clinicians (responsible for clinical assessment and measurement of temperature) and laboratory technicians (responsible for reading thick blood smears and determining parasite density) will be blinded to the treatment group assignments

Both the morning and evening doses of the study medication will be administered in the clinic. Study medications given to young children will be crushed, mixed with water, and administered as slurry. Study medications administered to older children and adults will be given as tablets or fractions of tablets to be taken orally with a glass of water. The study nurse will directly observe consumption of study medications. Patients will be observed for 30 minutes to ensure that the medications are not vomited. Any patient who vomits the medication within 30 minutes of administration will be retreated with a second dose. Any patient who vomits repeatedly (> 3 times) will be treated with/referred for treatment with parenteral quinine and recoded as having complicated malaria.

On day 0, the first dose of study medication will be administered before 11.00 a.m. and the second dose will be administered in the evening, approximately 8 hours later. On days 1 and 2, the first dose of study medication will be administered before 9.00 a.m. and the second dose will be administered in the evening, approximately 12 hours later.

Study participants will be free to either wait at the clinic or go home and return in the evening for the evening dose of study medications. Participants who opt to wait at the clinic shall wait in a specially designated waiting area. Participants will be reimbursed for transport to and from the clinic and for lunch (those who opt to wait at the clinic for the evening dose of medications). Home visitors shall actively follow patients who do not come for scheduled appointments.

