# Appendix 6a. Weight-based administration of study medications for AQ+AS group

| **Weight (kg)** | **Amodiaquine (AQ)**  **200 mg tabs (Base)** | | | **Artesunate (AS)**  **50 mg tabs** | | | **Placebo tablets** | | |
| --- | --- | --- | --- | --- | --- | --- | --- | --- | --- |
|  | **Day 0** | **Day 1** | **Day 2** | **Day 0** | **Day 1** | **Day 2** | **Day 0** | **Day 1** | **Day2** |
|  | **am** | **am** | **am** | **am** | **am** | **am** | **pm** | **pm** | **pm** |
| 10 | ½ | ½ | ¼ | ¾ | ¾ | ¾ | 1 | 1 | 1 |
| 11 | ½ | ½ | ¼ | 1 | 1 | 1 | 1 | 1 | 1 |
| 12 | ½ | ½ | ½ | 1 | 1 | 1 | 1 | 1 | 1 |
| 13 | ½ | ½ | ½ | 1 | 1 | 1 | 1 | 1 | 1 |
| 14 | ¾ | ½ | ½ | 1 ¼ | 1 ¼ | 1 ¼ | 1 | 1 | 1 |
| 15 | ¾ | ½ | ½ | 1 ¼ | 1 ¼ | 1 ¼ | 2 | 2 | 2 |
| 16 | ¾ | ¾ | ½ | 1 ¼ | 1 ¼ | 1 ¼ | 2 | 2 | 2 |
| 17 | ¾ | ¾ | ½ | 1 ½ | 1 ½ | 1 ½ | 2 | 2 | 2 |
| 18 | 1 | ¾ | ½ | 1 ½ | 1 ½ | 1 ½ | 2 | 2 | 2 |
| 19 | 1 | ¾ | ½ | 1 ½ | 1 ½ | 1 ½ | 2 | 2 | 2 |
| 20 | 1 | 1 | ½ | 1 ¾ | 1 ¾ | 1 ¾ | 2 | 2 | 2 |
| 21 | 1 | 1 | ½ | 1 ¾ | 1 ¾ | 1 ¾ | 2 | 2 | 2 |
| 22 | 1 ¼ | 1 | ½ | 1 ¾ | 1 ¾ | 1 ¾ | 2 | 2 | 2 |
| 23 | 1 ¼ | 1 | ½ | 2 | 2 | 2 | 2 | 2 | 2 |
| 24 | 1 ¼ | 1 ¼ | ½ | 2 | 2 | 2 | 2 | 2 | 2 |
| 25 | 1 ¼ | 1 ¼ | ½ | 2 | 2 | 2 | 3 | 3 | 3 |
| 26-27 | 1 ¼ | 1 | 1 | 2 ¼ | 2 ¼ | 2 ¼ | 3 | 3 | 3 |
| 28 | 1 ¼ | 1 ¼ | 1 | 2 ¼ | 2 ¼ | 2 ¼ | 3 | 3 | 3 |
| 29-31 | 1 ¼ | 1 ¼ | 1 | 2 ½ | 2 ½ | 2 ½ | 3 | 3 | 3 |
| 32 | 1 ½ | 1 ½ | 1 | 2 ½ | 2 ½ | 2 ½ | 3 | 3 | 3 |
| 33 | 1 ½ | 1 ½ | 1 | 2 ¾ | 2 ¾ | 2 ¾ | 3 | 3 | 3 |
| 34 | 1 ½ | 1 ½ | 1 ¼ | 2 ¾ | 2 ¾ | 2 ¾ | 3 | 3 | 3 |
| 35 | 1 ½ | 1 ½ | 1 ¼ | 2 ¾ | 2 ¾ | 2 ¾ | 4 | 4 | 4 |
| 36-37 | 1 ½ | 1 ½ | 1 ¼ | 3 | 3 | 3 | 4 | 4 | 4 |
| 38 | 2 | 1 ½ | 1 ¼ | 3 | 3 | 3 | 4 | 4 | 4 |
| 39 | 2 | 1 ½ | 1 ¼ | 3 ¼ | 3 ¼ | 3 ¼ | 4 | 4 | 4 |
| 40-43 | 2 | 2 | 1 | 3 ¼ | 3 ¼ | 3 ¼ | 4 | 4 | 4 |
| 44-47 | 2 | 2 | 1 ½ | 3 ½ | 3 ½ | 3 ½ | 4 | 4 | 4 |
| 48-49 | 2 | 2 | 2 | 3 ¾ | 3 ¾ | 3 ¾ | 4 | 4 | 4 |
| 50-59 | 2 ½ | 2 | 2 | 4 | 4 | 4 | 4 | 4 | 4 |
| >60 | 3 | 3 | 1 ½ | 5 | 5 | 5 | 4 | 4 | 4 |

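### The amodiaquine tablet table in Appendix 6a does not deliver the 10/10/5 mg/kg daily doses stated in section 6.4.1, by more than tablet rounding

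*Protocol*

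**What the plan says.** Section 6.4.1 gives the amodiaquine dose twice over: a three-day total of 25 mg/kg, and a daily split of "10 mg/kg on day 0, 10 mg/kg on day 1, and 5 mg/kg on day 2". It then adds: "Details of the dosing schedule are included in Appendix 6". Section 6.5 makes that appendix the working instruction: "Study medications will be administered according to weight-based guidelines (Appendix 6". Table 3 lists the tablet as "Amodiaquine (200mg base"), and the amodiaquine column head in Appendix 6a repeats the 200 mg strength.

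Appendix 6a lists amodiaquine tablets for Days 0, 1 and 2 by weight, in quarter-tablet steps. A child of 10 kg is listed for half a tablet on each of the first two days and a quarter on the last. A child of 12 kg is listed for half a tablet on every day. A child of 15 kg is listed for three quarters of a tablet on Day 0 and half on each later day.

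Appendix 6b uses the same tablet counts for the placebo dosed to match amodiaquine.

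**The concern.** The text presents the table as the detail of its own schedule, so the two should agree up to tablet rounding. In several rows the drop on Day 2 that defines a 10/10/5 regimen is absent: at 12, 13 and 48-49 kg all three days are equal.

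The nurse doses from the table, while a reader of the protocol or of a later report would take the regimen from section 6.4.1. The trial compares efficacy, safety and tolerability, and section 2.3 says its data go to the Ministry of Health for drug policy. The dose on each day is part of what defines the AQ+AS arm, and it is needed to interpret vomiting and other adverse events during the dosing days. A report of 10/10/5 mg/kg would misdescribe the treatment behind those results.

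**Working it through.** **Inputs.** Stated doses of 10, 10 and 5 mg/kg (section 6.4.1); 200 mg base per tablet (Table 3); tablets per day by weight (Appendix 6a). The table moves in quarter tablets, so one step is 200/4 = 50 mg, and rounding to the nearest step can miss by at most 25 mg.

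**Formulas.** For weight W in kg and t tablets on a given day:

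- dose in mg/kg = 200 × t / W
- deviation in mg = 200 × t − 10W on Days 0 and 1, and 200 × t − 5W on Day 2

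**Where the text reproduces.** At 10 kg, ½, ½ and ¼ tablet give 100/10, 100/10 and 50/10 = 10/10/5 mg/kg. The 20 kg row also agrees exactly.

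**Where it does not.**

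| Weight (kg) | Tablets, Days 0/1/2 | mg/kg, Days 0/1/2 | Deviation (mg) | Total (mg/kg) |
|---|---|---|---|---|
| 12 | ½, ½, ½ | 8.3 / 8.3 / 8.3 | −20, −20, +40 | 25.0 |
| 13 | ½, ½, ½ | 7.7 / 7.7 / 7.7 | −30, −30, +35 | 23.1 |
| 15 | ¾, ½, ½ | 10.0 / 6.7 / 6.7 | 0, −50, +25 | 23.3 |
| 26 | 1¼, 1, 1 | 9.6 / 7.7 / 7.7 | −10, −60, +70 | 25.0 |
| 34 | 1½, 1½, 1¼ | 8.8 / 8.8 / 7.4 | −40, −40, +80 | 25.0 |

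**Count against rounding, 10 to 35 kg.** Of 26 whole-kilogram weights, 18 have at least one day more than 25 mg off: 12-15, 18, 19, 22, 23 and 26-35 kg. At 9 of these (15, 26-31, 34 and 35 kg) a day is off by a full quarter tablet (50 mg) or more.

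**Range of daily error, 10 to 35 kg.**

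- Day 0: −23% (13 kg) to +14% (22 kg)
- Day 1: −33% (15 kg) to +4% (24 kg)
- Day 2: −20% (25 kg) to +67% (12 kg)
- Three-day total: 22.6 to 25.0 mg/kg

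**Whole table.** Of 31 weight rows (the last taken at 60 kg), 10 match 10/10/5 within rounding at some weight in the row and 21 do not. Totals over all weights are 22.0 to 26.0 mg/kg.

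**Does holding the total explain it?** For each weight the table's own tablet total was kept, and every quarter-tablet division of it was compared with 10/10/5 by the sum of squared deviations. At 14 of the 26 weights (12-15 and 26-35 kg) a closer division exists. At 26 kg, for instance, the largest daily deviation with the same 3¼ tablets could be 20 mg instead of 70 mg. This tests the rounding explanation and proposes no dose.

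**Internal irregularity.** The Day-1 dose falls from 1¼ tablets at 25 kg to 1 tablet at 26-27 kg and returns to 1¼ at 28 kg. The Day-2 dose doubles from ½ to 1 tablet between 25 and 26 kg.

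**Reading error?** The placebo columns of Appendix 6b repeat the pattern, so a fault in extracting one table from the PDF is not the explanation.

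**The case against.** The best counter-argument is that section 6.4.1 puts the 25 mg/kg total first and the daily split in parentheses, and that the table was built to honour the total. From 10 to 35 kg the table's total is the largest quarter-tablet total not exceeding 25 mg/kg at 24 of 26 weights (all but 30 and 31 kg). Rounding each day separately would break the total: it gives 20.8 mg/kg at 12 kg and 27.8 mg/kg at 18 kg. This stands for 18, 19, 22 and 23 kg, where no division of the same tablets is closer to 10/10/5 than the printed one. It fails for the other 14 weights.

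The percentages also sound larger than the tablets involved: +67% at 12 kg is 40 mg and −33% at 15 kg is 50 mg, about one quarter tablet each. That is true, but these are small children and the deviation per kilogram is what the text specifies.

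Finally, section 6.5 makes clear that the nurse follows Appendix 6, every AQ+AS patient of a given weight gets the same tablets, and the placebo matches. So the randomised comparison, the primary outcome and the sample size do not depend on the split. This stands too, and it limits the severity. It does not remove the conflict, because the protocol still states daily doses that its own table does not give.

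**Conclusion.** The concern holds. The three-day total of about 25 mg/kg is respected, but the daily split is not. From 10 to 35 kg, 18 of 26 weights differ from 10/10/5 by more than quarter-tablet rounding, and 14 of those differ even after allowing the table to hold its total. Eight of the 26 match.

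The 10-35 kg range is an assumption about where most children aged 1 to 10 years will fall. The protocol gives no weight distribution, so the share of patients affected cannot be stated. No effect on efficacy is shown. The defect lies in the description of the intervention and should be corrected; it does not threaten the validity of the comparison.

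**What to change.** Reconcile section 6.4.1, the amodiaquine columns of Appendix 6a and the matching placebo columns of Appendix 6b before enrolment, including the irregular Day-1 and Day-2 steps around 25-28 kg. Whether the text or the table is right is for the clinicians. Whichever is kept, the report should give the amodiaquine mg/kg actually administered on each day, computed from recorded weight and tablets, and should not simply cite 10/10/5. The cost is an amendment to wording or to a table; no extra data are needed.

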## 6.5 Treatment administration and blinding

Study medications will be administered according to weight-based guidelines (Appendix 6). Study medications will not be identical in appearance or taste, but the number of doses received will be similar (2 different medicines in the morning, 1 medicine in the evening) for patients in both treatment groups. Patients will not be informed of their treatment regimen, and all study staff involved in the assessment of patient outcomes, including the study clinicians (responsible for clinical assessment and measurement of temperature) and laboratory technicians (responsible for reading thick blood smears and determining parasite density) will be blinded to the treatment group assignments

Both the morning and evening doses of the study medication will be administered in the clinic. Study medications given to young children will be crushed, mixed with water, and administered as slurry. Study medications administered to older children and adults will be given as tablets or fractions of tablets to be taken orally with a glass of water. The study nurse will directly observe consumption of study medications. Patients will be observed for 30 minutes to ensure that the medications are not vomited. Any patient who vomits the medication within 30 minutes of administration will be retreated with a second dose. Any patient who vomits repeatedly (> 3 times) will be treated with/referred for treatment with parenteral quinine and recoded as having complicated malaria.

On day 0, the first dose of study medication will be administered before 11.00 a.m. and the second dose will be administered in the evening, approximately 8 hours later. On days 1 and 2, the first dose of study medication will be administered before 9.00 a.m. and the second dose will be administered in the evening, approximately 12 hours later.

Study participants will be free to either wait at the clinic or go home and return in the evening for the evening dose of study medications. Participants who opt to wait at the clinic shall wait in a specially designated waiting area. Participants will be reimbursed for transport to and from the clinic and for lunch (those who opt to wait at the clinic for the evening dose of medications). Home visitors shall actively follow patients who do not come for scheduled appointments.

## 6.6 Additional medications

On day 0, patients will receive paracetamol (10mg/kg) to take every 8 hours until the resolution of fever. Patients found to have uncomplicated malaria and a concomitant illness will be treated for both and followed up according to the study protocol. For patients with anaemia (Hb < 10 g/dL), we will follow Integrated Management of Childhood Illness (IMCI) guidelines: anaemic children will be treated with iron sulphate (100 mg po qD for 2 weeks) and mebendazole (only children > 1 year of age; 250 mg age 1-2 years; 500 mg > 2 years age; treated no more frequently than every 6 months).

# 7.0 FOLLOW-UP EVALUATION AND PROCEDURES

## 7.1 Follow-up schedule

Patients will be asked to return to the clinic for follow-up on days 1, 2, 3, 7, 14, 21, 28, and any unscheduled day that they feel ill. All patients will be reimbursed the cost of their transport to and from the clinic. At enrolment, details about the location of the patient’s residence will be obtained and if a subject does not return for a scheduled clinic follow-up appointment, the study personnel shall visit them at home. Patients who return on day 1 and fail to fulfil the criteria of *P. falciparum* mono-infection with a parasite density of > 2000 parasites/ul and < 200,000 parasites/ul will be excluded from further study and referred to OPD for management. At each repeat visit, temperature will be measured and a focused physical examination will be performed. A finger prick blood sample will be obtained on days 2, 3, 7, 14, 21 and 28 (and any extra day) to repeat thick blood smears and to save on filter paper. Haemoglobin will be re-evaluated on day 28 or at the time of clinical treatment failure.

# Table 4. Follow-up Schedule

|  | **Day 0** | **Day 1** | **Day 2** | **Day 3** | **Day 7** | **Day 14** | **Day 21** | **Day 28** | **Extra Day** |
| --- | --- | --- | --- | --- | --- | --- | --- | --- | --- |
| **Study medications** | X | X | X |  |  |  |  |  |  |
| **History** | X | X | X | X | X | X | X | X | X |
| **Temperature measurement** | X | X | X | X | X | X | X | X | X |
| **Physical exam** | X | X | X | X | X | X | X | X | X |
| **Thick blood smear** | X |  | X | X | X | X | X | X | X |
| **Thin blood smear** | X |  |  |  |  |  |  |  |  |
| **Filter paper sample** | X |  | X | X | X | X | X | X | X |
| **Haemoglobin** | X | † | † | † | † | † | † | X | † |
| **Assessment for adverse drug event** | X | X | X | X | X | X | X | X | X |

X = perform this task

† Performed on day of clinical failure

## 7.2 Classification of treatment outcome and management of treatment failure

Patients will be followed for 28 days and will have treatment outcomes assessed according to the WHO 2003 guidelines (Appendix 7). Patients who require clinical rescue therapy (ETF, LCF, or LPF) will be treated with quinine 10 mg/kg orally three times a day for 7 days. Any patient who is diagnosed with severe malaria or danger signs during follow-up, will be referred for appropriate treatment with parenteral quinine at the local facility or hospital. Patients not admitted to the hospital will receive oral quinine to complete a 7-day course of therapy. If a patient requires clinical rescue therapy, formal study follow-up will end, and the patient will be followed up at the discretion of the study physician. Haemoglobin measurement will be repeated on the day the patient receives clinical rescue therapy.

## 7.3 Exclusion after enrollment and loss to follow-up

Patients will be excluded from the study and not have their treatment outcome assessed if any of the following occurs after enrollment:

- 1. Use of antimalarial drugs outside of the study protocol.
  2. Development of a febrile illness (e.g. pneumonia, dysentery, measles) concomitantly with parasitaemia which interferes with outcome classification.
  3. Withdrawal of informed consent.
  4. Loss to follow-up: Patients who fail to attend a follow-up visit and are unable to be located within 24 hours on Days 1-3 or within 48 hours on Days 4-28.

## 7.4 Management of non-malarial illnesses

Patients who are found to have illnesses other than malaria during standard 28-day follow-up will receive standard-of-care treatment in the clinic, according to standardized algorithms, or will be referred to OPD for the appropriate care. Routine use of non-study medications with antimalarial activity, including tetracycline, antifolate, and macrolide antibiotics, will be avoided when acceptable alternatives are available.

# 8.0 ASSESSMENT FOR ADVERSE EVENTS

## 8.1 Definitions

An adverse event is defined as "any untoward medical occurrence in a patient or clinical investigation subject administered a pharmaceutical product that does not necessarily have a causal relationship with this treatment" (ICH Guidelines E2A). An adverse event can further be broadly defined as any untoward deviation from baseline health which includes:

- Worsening of conditions present at the onset of the study
- Deterioration due to the primary disease
- Intercurrent illness
- Events related or possibly related to concomitant medications

(International Centers for Tropical Disease Research Network Investigator Manual, Monitoring and Reporting Adverse Events, 2003).

A serious adverse event is defined as an experience that results in any of the following outcomes:

- Death during the period of study follow-up
- Life-threatening experience (one that puts a patient at immediate risk of death at the time of the event)
- Inpatient hospitalization during the period of study follow-up
- Persistent or significant disability or incapacity
- Specific medical or surgical intervention to prevent one of the other serious outcomes listed in the definition.

## 8.2 Identification of adverse events

At each follow-up visit (days 1, 2, 3, 7, 14, 21, 28, and any unscheduled day), study clinicians will assess patients according to a standardized clinical record form (appendix 12). A severity grading scale, based on toxicity grading scales developed by the WHO and the National Institutes of Health, Division of Microbiology and Infectious Diseases, will be used to grade severity of all symptoms, physical exam findings, and haemoglobin results (Appendices 9). Any new event, or an event present at baseline that is increasing in severity, will be considered an adverse event.

## 8.3 Reporting of adverse events

For each possible adverse event identified and graded as moderate, severe or life threatening, an adverse event report form will be completed (Appendix 12). An adverse event report form will not be completed for events classified as mild as these symptoms are common and difficult to distinguish from signs and symptoms due to malaria. The following information will be recorded for all adverse experiences that are reported:

1. Description of event
2. Date of event onset
3. Date event reported
4. Maximum severity of the event
5. Maximum suspected relationship of the event to study medication
6. Is the event serious?
7. Initials of the person reporting the event
8. Was the event episodic or intermittent in nature?
9. Outcome
10. Date event resolved

## 8.4 Reporting of serious adverse events

Guidelines for reporting of serious adverse events provided by the UCSF Committee for Human Research and the Ugandan National Council for Science and Technology will be followed.

# 9.0 STATISTICAL CONSIDERATIONS

## 9.1 Sample size calculations

The sample size calculations will be made for the study based on the estimated efficacy of the combination regimens to be studied in the given regions. For the purposes of sample size calculation, the risk of clinical rescue therapy will be the primary outcome. If the null hypothesis states that there is no difference in clinical outcome between the treatment groups, we plan to test the alternative hypothesis that treatment with an alternative combination regimen will decrease the likelihood of clinical failure at 28 days of follow-up. The risk of clinical rescue therapy with AQ+AS is estimated to be 40-50% based on previous data (UMSP, unpublished data). We plan to enroll 200 patients in each treatment arm at all of the study sites (400 patients per site, 1600 patients total). Based on an α = 0.05 (two-sided) and a power of 80%, allowing for 10% loss to follow-up, we will have the ability to detect a risk difference of approximately 15% between the two treatment groups.

